#### 11.4. Adverse Event Reporting Period

The AE reporting period for this study begins at the time of administration of FDG and continues until 30 days after the administration of FDG or at death if it occurs earlier.

In addition, any known untoward event of Grade 3 or greater severity that occurs subsequent to the AE reporting period that the Investigator assesses as Possibly, Probably or Very Likely related to the administration of FDG should be reported as an SAE.

All AEs and SAEs must be followed until resolution unless, in the investigator's opinion, the condition is unlikely to resolve because of the subject's underlying disease.

Patients withdrawn from the study due to an AE will be followed until the AE has resolved. In the case of an SAE, the patient will be followed until clinical recovery or until progression has been stabilized or judged to be chronic.

#### 11.5. Serious Adverse Event Reporting to OCOG

Adverse events considered to be **SERIOUS and UNEXPECTED and RELATED** (i.e., attributed as Possibly, Probably, or Very Likely related) to the administration of FDG, must be reported by the Investigator to OCOG within 24 hours from the time when the clinical centre personnel became aware of the event. All other SAEs should be reported to OCOG within 5 days from the time when the clinical centre personnel became aware of the event.

Follow-up reports must be submitted to OCOG when new information becomes available and not later than 5 days after the clinical centre personnel became aware of the event. If an ongoing SAE changes in its intensity (Grade) or relationship to the Investigational Product, a follow-up SAE report should be sent immediately.

In the rare event that the Investigator does not become aware of the occurrence of an SAE immediately, the Investigator is to report the event to OCOG within 24 hours of notification of the event.

The occurrence of SAEs and follow-up information related to SAEs will be documented by the clinical centre using the OCOG SAE Form. Relevant source documentation should be included. Forms and source documentation must be submitted by confirmed facsimile transmission (fax) and the original mailed to OCOG.

### 11.6. Serious Adverse Event Reporting to Health Canada

OCOG, acting as Sponsor, will be responsible for notifying Health Canada, Biologics and Genetic Therapies Directorate (BGTD) in an expedited manner of adverse events which are considered **SERIOUS and UNEXPECTED and RELATED** to the administration of FDG (or for which a causal relationship with the administration of FDG cannot be ruled out). For each event reported to Health Canada, OCOG will inform the DSMB.

Follow-up of SAEs as documented and submitted by the clinical centre on the OCOG SAE form will be forwarded to Health Canada by OCOG, where applicable.

### 11.7. Reporting SAEs to Local Research Ethics Boards

Investigators will be notified by OCOG of all SAEs that were reported to Health Canada and will be instructed to notify their local REB/IRB of the same, as per local REB/IRB requirements. The submission of these events by the investigator to their local REB/IRB should be completed upon receipt and not later than 30 days from the date of the correspondence from OCOG.

The Investigator will be responsible for reporting SAEs occurring at their local site to their local REB/IRB, as per local REB/IRB requirements.

## 12. STUDY OUTCOMES

### 12.1. Primary Outcome

The primary outcome is treatment delivered. Any patient who does not complete treatment as scheduled due to adverse events, withdrawal, or other reasons, will have treatment delivered defined as the treatment planned. The actual treatment delivered will be classified into one of the following three categories:

- (1) standard pelvic chemo-radiotherapy of curative intent (i.e. not palliative care nor extended field radiation therapy). This will include all brachytherapy volumes and doses.
- (2) more extensive chemo-radiotherapy of curative intent, such as EFRT, either with or without biopsy. EFRT includes any treatment extending outside the standard pelvic RT field as defined in Table 5, including para-aortic or upper common iliac lymph nodes, or distal vagina.
- (3) therapy with palliative or non-curative intent for example, symptom management, chemotherapy, radiotherapy or both.

It is conceivable that by allowing patients with pre- randomization CT scans to be eligible for the study bias could be introduced. Patients who had distant metastases e.g. liver documented on CT scan would not be referred for the trial; whereas patients with a normal liver on CT prior to randomization would be referred to the trial and that CT would be considered as the “usual intervention”. For patients who did not have a pre-randomization

CT and who were allocated to PET-CT, the contrast-enhanced CT could detect any liver metastases, thus favoring the PET arm. We feel that such a bias is unlikely because liver metastases is a rare occurrence in cervix cancer.

## 12.2. Secondary Outcomes

Secondary Outcomes are:

1. **Event-free Survival (EFS):** EFS is calculated from the date of randomization to the date of objective disease recurrence, or objective disease progression or death due to any cause following study treatment. The EFS of patients alive and without disease recurrence or progression at the time of analysis will be censored on the last clinic follow-up date. Suspicion of recurrent or progressive disease will be verified with further investigations as per the centre's practice. Objective disease recurrence or progression will be defined as a positive result on a biopsy of clinical disease or by disease progression on radiologic imaging.
2. **Overall Survival (OS):** OS is calculated as the date from randomization to the date of death due to any cause. Patients alive at the time of analysis will be censored on the last date the patient is confirmed to be alive.
3. **Standardized Uptake Value (SUV):** The SUVs of the PET-CT cervical cancer scans will be used to assess their ability to predict EFS and OS.
4. **Economic and Quality of Life Analyses** (see *Appendices IV, V and IX*)

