### **10.2. Follow-up Assessment**

Patient follow-up care will be at the discretion of the investigator at the local site. It is suggested that follow-up care be in accordance with the Cancer Care Ontario guidelines. For the purposes of collection of study related data, patients will be followed for approximately 5 years. Assessments will be calculated from the date of randomization.

Patients will be assessed every 6 months ( $\pm 14$  days) for the first 2 years (Year 1 and 2). At each follow-up visit, patients will be required to return to the clinic to assess current disease status. ECOG performance status will also be assessed and documented. The two QoL questionnaires (EORTC QLQ-30 version 3 and QLQ-CX24) will be completed by the patient at 3, 6, 12, 18 and 24 months after randomization. These questionnaires can be either mailed to the patient or completed by the patient at a clinic visit (see *Appendix IV*).

To perform the health economic evaluation, a limited set of questions on health care resource utilization and patient utility will be incorporated into the data collection. The health utility questionnaire (EQ-5D) will be completed by the patient at 3, 6, 12, 18 and 24 months after randomization. This questionnaire can be either mailed to the patient or completed by the patient at a clinic visit (see *Appendix V*).

Information on a patient's cancer status (free of disease or not) and overall survival will be abstracted from their cancer centre or hospital records, or by contacting the family physician at least once a year for Years 3, 4, and 5.

On completion of the 5 years of follow-up required by this study, further assessment of the patient will be according to the oncologist's or local institutional practice; patients will not be restaged at the end of the 5-year follow-up period.

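### EFS is censored at the last clinic visit although status in Years 3–5 may come from records or the family physician, so Kaplan-Meier EFS after month 24 is biased low

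*Protocol*

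**What the plan says.** Protocol section 12.2 measures EFS from randomization to "objective disease recurrence, or objective disease progression or death due to any cause following study treatment". Nothing limits events to those found at a clinic visit. Patients alive and free of recurrence or progression "at the time of analysis will be censored on the last clinic follow-up date".

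The OS rule in the same section differs: "Patients alive at the time of analysis will be censored on the last date the patient is confirmed to be alive". That date may come from any source.

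Section 10.2 sets six-monthly assessments "for the first 2 years (Year 1 and 2). At each follow-up visit, patients will be required to return to the clinic". From Year 3 the source changes: "cancer status (free of disease or not) and overall survival will be abstracted from their cancer centre or hospital records". The alternative route that the section allows is to obtain the same information "by contacting the family physician at least once a year for Years 3, 4, and 5". Appendix III agrees, listing disease status every six months in Years 1 and 2, then EFS and OS annually in Years 3 to 5.

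Section 13.1 calls EFS and OS the longer-term question, names the 5-year values, and plans Kaplan-Meier curves by arm with Cox models for the comparison.

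**The concern.** After month 24 the annual abstraction or physician contact does two jobs: it reports events and it confirms that patients are event-free. The censoring rule uses only the first. Take two patients last seen in clinic at month 24. One recurs at month 40, and her physician reports it: she stays at risk to month 40 and counts as an event. The other is confirmed disease-free at month 60 by the same route: she leaves the risk set at month 24. Whether someone stays at risk between months 24 and 60 then depends on whether she later has the event. Kaplan-Meier and Cox methods assume that it does not.

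At stake is the absolute EFS curve in Years 3 to 5, which determines the 5-year figure. EFS is the first secondary objective and one of the two outcomes in the SUV analysis.

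A smaller wording point sits in the same definition. It counts "or death due to any cause following study treatment", although time starts at randomization and section 13.3 analyses everyone randomized. Read literally, a death between randomization and treatment is not an event, and the censoring sentence does not cover it either, because that sentence concerns patients who are alive.

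**Working it through.** The protocol gives no EFS rate, event count or power for EFS, so there is no EFS figure to reproduce. Its only power statement (section 13.2: 192 versus 96 patients, 45% versus 25%, Fisher's exact test, over 90%) concerns the primary outcome. Exact enumeration gives 91.5%, so that figure holds and this point does not bear on it.

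**Inputs**
- From the protocol: the censoring rule (12.2), the last required clinic visit at 24 months and the later data sources (10.2), and the 5-year horizon and methods (13.1).
- Assumed: true EFS S(t), and q, the share of patients event-free at 5 years whose last clinic date is month 24. The others are taken as censored at 5 years, and every event is taken as captured.

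**Formula.** At time u between 2 and 5 years, the share of the cohort still at risk is S(u) − q·S(5), because the wrongly censored patients have left. Integrating the resulting hazard from year 2 to year 5 gives the large-sample Kaplan-Meier value:

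estimate(5) = S(2) · (1 − q) · S(5) / (S(2) − q · S(5))

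**Numbers.** Take S(5) = 0.60 with constant hazard, so S(2) = 0.60^(2/5) = 0.815.
- q = 0: 0.600, as it should be.
- q = 0.10: 0.815 × 0.54 / (0.815 − 0.06) = 0.583.
- q = 0.25: 0.815 × 0.45 / (0.815 − 0.15) = 0.551.
- q = 0.50: 0.815 × 0.30 / (0.815 − 0.30) = 0.475.

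At smaller q the effect is slight: 59.7% at q = 2% and 59.2% at q = 5%.

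**Sensitivity.** With S(5) from 50% to 70% and Weibull shape from 0.6 to 1.0, the downward bias is about 1 to 2 points at q = 10%, 3 to 5 at q = 25%, and 9 to 13 at q = 50%.

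**Hazard ratio, equal q in both arms.** In 1,000 simulated trials per setting (192 versus 96 patients, control 5-year EFS 60%, Weibull shape 0.8), a null ratio stayed at about 1.00 for q = 25%, 50% and 100%. A true ratio of 0.75 came out at about 0.75 for q = 25% and 50%, and at 0.84 for q = 100%.

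**Hazard ratio, unequal q.** In separate large simulations with no true difference, q of 30% with PET-CT and 50% with CT gave a ratio of about 0.87 to 0.88. Reversing the shares gave 1.16.

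**The case against.** The strongest reply is that clinic follow-up need not mean a visit required by the study. Section 10.2 leaves follow-up care to the investigator, suggests a provincial guideline, and names cancer centre or hospital records first among the sources for Years 3 to 5. Those records would often contain routine oncology visits after month 24, and Appendix III plainly intends EFS to be updated each year. On that reading a patient seen in clinic in Year 4 is censored in Year 4, q is small, and so is the bias. This stands as a limit on size. It does not remove the defect, because physician contact is a permitted source that is not a clinic visit, and a record can document status without one.

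A reader might infer that 5-year EFS collapses. The formula does give 0 at q = 1, but that needs every event-free patient to have no clinic date after month 24, and nothing in the protocol suggests it.

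A reader might also infer that the rule favours PET-CT in the hazard ratio. That needs q to be larger in the CT arm, and the protocol gives no reason to expect so. If palliative patients were the ones missing clinic, section 13.2 anticipates more of them with PET-CT (20% versus 10%), which points the other way. Many of them may also have an event early and never enter q. The direction is unknown.

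On deaths before treatment, the qualifier may simply describe the follow-up period. The randomization start and the intention-to-treat set favour counting every death, OS counts them all, and the protocol gives no number of such deaths. This is a wording conflict and no evidence of a material loss of events.

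**Conclusion.** The rule as written censors by outcome after month 24, and its effect on absolute EFS is downward. That follows from sections 12.2 and 10.2 whenever some event-free patients have their latest status from a non-clinic source. The size is not fixed by the protocol. It is a point or two if about 10% of event-free patients lack a later clinic date, and around 9 to 13 points if half do, under the assumed EFS of 50% to 70%. The between-arm comparison is little affected unless q differs by arm or approaches 1.

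Severity is moderate. EFS is a secondary outcome with no stated power. The primary outcome, the sample size, the interim rule in section 13.6 (which uses treatment delivered) and OS do not depend on this sentence. The treatment qualifier on EFS events is a minor wording correction.

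**What to change.** In section 12.2, censor EFS at the last date on which the patient was documented free of recurrence or progression from any permitted source: clinic visit, record abstraction or physician contact. This brings EFS into line with the OS rule, and events and event-free status then come from the same sources. Record that date, with its source, at each annual update in Years 3 to 5.

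In the same section, delete the last three words of "or death due to any cause following study treatment" so that any death after randomization is an EFS event, consistent with the time origin and the Full Analysis set.

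The cost is two edits to one definition and a date (with source) on the annual follow-up form. No change to sample size or visits is needed, and it should be done before EFS is analysed. For abstractions already made, the status date can be taken from the record or contact log.

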## 13. STATISTICAL CONSIDERATIONS

### 13.1. Statistical Analysis

The primary outcome is treatment delivered. Exact tests will be used to investigate a difference in the proportion of patients receiving standard pelvic chemo-radiotherapy of curative intent, more extensive chemo-radiotherapy of curative intent or therapy with palliative or non-curative intent both unadjusted (e.g. exact  $\chi^2$  test) and after adjusting for the stratification factors (e.g. logistic regression). A secondary analysis will explore the specific treatments delivered (e.g. brachytherapy dose and volume, parametrial boost doses, external radiation dose and volume, fractions, overall treatment duration, radiotherapy technique – IMRT versus conventional radiotherapy, chemotherapy dose and duration) using descriptive statistics.

The longer term question concerns the subsequent EFS and OS of patients following EFRT. If, as anticipated, the PET-CT strategy is able to generate a cohort of patients who have para-aortic nodal disease that is curable by EFRT, then the 5-year EFS and OS of patients following surgery would be expected to be higher for patients in the CT abdomen and pelvis + whole body PET-CT group *versus* the CT abdomen and pelvis group. EFS and OS will be estimated and plotted for each arm separately using Kaplan-Meier methods; the treatment arms will be compared using Cox proportional hazards regression models.

The prognostic ability of PET SUV of cervical cancer will be investigated as a risk factor for EFS and OS using Cox proportional hazards regression models amongst those patients

undergoing PET-CT only. Economic and Quality of Life analyses are described in Appendices IV, V and IX.

Some missing data is expected for economic outcomes and will be assumed to be missing at random. Missing data will be left as missing for other outcomes (e.g. baseline information) and descriptive statistics will be used to report the number of missing results. Missing data is not expected to occur for the primary outcome except in cases where patients withdraw from the study or rapidly deteriorate. In this case, the planned treatment will be used in lieu of treatment delivered.

All tests will be two-sided and based on an intent-to-treat analysis. A p-value of 0.05 or less will be considered statistically significant. In addition, 95% confidence intervals will be constructed for outcomes of interest. All data analysis will be performed using the latest versions of SAS (Cary, NC) and using StatXact (Boston, MA).

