## 1.6. Upstaging and Treatment

When the pelvic nodes and para-aortic nodes are normal on imaging, patients receive pelvic RT (45-50 Gy by external beam to the level of L5/S1 plus brachytherapy) and weekly cisplatin-based chemotherapy. The detection of tumour in the common iliac or para-aortic nodes by an imaging test leads to a change in the RT volume of the combined modality treatment (suggested treatments indicated in Table 5). Patients receive pelvic RT and para-aortic RT (40-45 Gy) to include para-aortic nodes to the T12/L1 level. This RT is also referred to as extended field RT (EFRT). The addition of EFRT increases the side effects of treatment e.g. 3% major toxicity to the small bowel. If imaging detects disease in the common iliac nodes, the pelvic RT fields are altered to include the next echelon lower para-aortic nodes up to L1/L2. The detection of tumour in the pelvic nodes may also lead to a change in treatment with an increase in the pelvic RT field to the L4 level. Finally, if imaging detects distant disease e.g. supraclavicular or mediastinal nodes, bone, liver, or lung, the patient is no longer a candidate for combined modality chemo-RT and can receive symptom management and/or palliative care. In some cases, PET-CT may downstage nodes or metastatic sites thought to be involved on the basis of CT, resulting in less extensive treatment.

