**Table 5: Recommended Changes in Therapy**

| Imaging                                                                        | Recommended treatment                                                                                     |                                                                                               |
|--------------------------------------------------------------------------------|-----------------------------------------------------------------------------------------------------------|-----------------------------------------------------------------------------------------------|
| Disease in Para-aortic nodes                                                   | EFRT                                                                                                      | Extend radiation field to include Para-aortic nodes to T12/L1                                 |
| Disease identified in pelvic nodes or presacral nodes                          |                                                                                                           | Extend superior pelvic margin to include common iliac nodes to L4 and/or include whole sacrum |
| Disease identified in common iliac nodes                                       |                                                                                                           | Extend superior pelvic field margin to include low Para-aortic nodes i.e., L1/2               |
| Extensive disease identified in primary cervix tumor or pelvic nodes           | Modify pelvic radiation fields without EFRT                                                               |                                                                                               |
| More extensive cervical disease e.g. uterine extension                         | Change brachytherapy volume or dose                                                                       |                                                                                               |
| Supraclavicular nodes, mediastinal nodes, bony mets, other solid organ disease | Palliative care only ie., chemo alone or palliative radiation therapy, clinical trials or supportive care |                                                                                               |

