## 5. PRE-TREATMENT EVALUATION

### *Refer to Appendix III: Schedule of Study Assessments and Evaluations*

The Baseline assessment is to include documentation of cancer staging as per FIGO staging criteria (see **Appendix I**). The presence of relevant comorbidities and ECOG performance status is to be recorded. Physical exam will include the assessment of height and weight.

Other baseline assessments will include: a chest X-ray (or chest CT scan) and blood tests (creatinine and random blood sugar) within a 28 day period prior to randomization. Pelvic MRI as performed according to local centre practice will be documented and utilized for stratification at the time of randomization. Patients may or may not have had a contrast-enhanced CT scan of the abdomen and pelvis at the time of randomization. If a patient has had a contrast-enhanced CT scan of the abdomen and pelvis it must have been done within 6 weeks of randomization. Otherwise, the CT scan needs to be repeated (see **Section 7.2** for minimum standards and **Appendix VI, item 6.** for contrast-enhanced CT scan procedures).

The QoL questionnaires (EORTC QLQ-30 version 3 and EORTC QLQ-CX24, see **Appendix IV**) and the questionnaire to measure health utilities (EQ-5D, see **Appendix V**) are to be completed by the patient after informed consent has been obtained. It is preferable for the patient to complete these questionnaires prior to randomization, although this is not mandatory.

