## 6. RANDOMIZATION

Patients will be allocated to one of two imaging groups:

| Study Group | Intervention                                                      |
|-------------|-------------------------------------------------------------------|
| 1           | CT Abdomen and Pelvis* + whole body PET-CT†
(Experimental arm) |
| 2           | CT Abdomen and Pelvis* (Standard arm)                             |

\* Usual strategy is contrast-enhanced CT of abdomen and pelvis

† If contrast-enhanced CT of abdomen and pelvis has been done prior to randomization, then a low resolution CT is done with the PET. If a contrast-enhanced CT of abdomen and pelvis was performed within 6 weeks prior to randomization, it is not repeated.

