### 6.1. Stratification

Eligible, consenting patients will be stratified by:

- (1) Pre-randomization CT scan abdomen and pelvis *versus* no pre-randomization CT scan abdomen and pelvis
- (2) Pre-treatment pelvic MRI *versus* no pelvic MRI
- (3) Stage of cervical cancer (Stage IB through IIA *versus* Stage IIB through IVA)
- (4) Treatment centre.

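### The adjusted primary analysis uses whether a pre-randomization CT was done but not what it showed, so it gives up some precision; this is a low-severity point that is cheap to mend

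*Protocol*

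**What the plan says.** Section 13.1 plans the comparison of treatment delivered in two forms: an unadjusted exact test, and an analysis "after adjusting for the stratification factors (e.g. logistic regression". The example in brackets is about the method; the covariates are fixed as the stratification factors. Section 6.1 lists four: CT before randomization or not ("Pre-randomization CT scan abdomen and pelvis" against "no pre-randomization CT scan abdomen and pelvis"), pelvic MRI done or not, stage group, and centre. None of them records an imaging finding.

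Section 5 allows for both situations: "Patients may or may not have had a contrast-enhanced CT scan of the abdomen and pelvis at the time of randomization". Section 6 adds: "If a contrast-enhanced CT of abdomen and pelvis was performed within 6 weeks prior to randomization, it is not repeated". Section 12.1 treats such a scan as the usual intervention. On the link to the outcome, Section 1.6 says: "The detection of tumour in the common iliac or para-aortic nodes by an imaging test leads to a change in the RT volume". For para-aortic disease Table 5 recommends: "Extend radiation field to include Para-aortic nodes to T12/L1". Treatment beyond the standard pelvic field is category 2 of the primary outcome in Section 12.1.

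**The concern.** For a woman whose study CT precedes allocation, the CT finding is a true baseline value. It lies on the protocol's own route from imaging to the outcome category. The yes/no factor tells the model that a scan exists but not whether it already pointed to extended-field treatment. No other listed factor fully replaces it: the staging rules in Appendix I say CT findings should not change the clinical stage, and the MRI factor is also only done or not done.

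The difference in treatment between CT-positive and CT-negative women is not caused by PET-CT, yet it stays in the residual variation around the PET-CT effect. What is at stake is the width of the confidence interval, and the power if the true difference is smaller than the 20 points planned for.

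**Working it through.** **Inputs from the protocol (Section 13.2).** EFRT or palliative care: 25% in the CT arm (about 15% EFRT, 10% palliative) and 45% in the PET-CT arm; 96 and 192 patients; two-sided 0.05; Fisher's exact test. The check uses this two-way split, standard against non-standard treatment.

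**The plan's own figure.** Exact enumeration of Fisher's test at 96 and 192 gives 91.5% power, so the statement of over 90% holds.

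**Assumptions not in the protocol.**
- f, the share with a prior CT: 25%, 50%, 75%.
- q, the share of those scans showing disease beyond the standard pelvic field: 15%, equal to the plan's EFRT rate in the CT arm; 10% as a low case.
- r, the chance of non-standard treatment if CT-positive, the same in both arms: 90%, 70%, and 60% as a low case.
- Overall rates are 25% and 45% both with and without a prior CT, so the yes/no CT factor by itself explains nothing.

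**Unadjusted variance of the risk difference.** 0.45×0.55/192 + 0.25×0.75/96 = 0.001289 + 0.001953 = 0.003242; SE 5.69 points.

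**Variance when stratified by CT result.** Sum over strata of w[p1(1−p1)/192 + p0(1−p0)/96], where w is the stratum's share of patients. The strata are no prior CT (w = 1−f), prior CT positive (w = fq) and prior CT negative (w = f(1−q)). The rate in CT-negative women is (overall rate − qr)/(1−q).

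**Worked case, f = 50%, q = 15%, r = 90%.**
- CT-negative rates: (0.25 − 0.135)/0.85 = 13.5% in the CT arm; (0.45 − 0.135)/0.85 = 37.1% in the PET-CT arm.
- Average within-stratum variance among women with a prior CT: 0.15×0.09 + 0.85×0.1170 = 0.1129 (CT arm); 0.15×0.09 + 0.85×0.2333 = 0.2118 (PET-CT arm).
- Total: (0.5×0.2475 + 0.5×0.2118)/192 + (0.5×0.1875 + 0.5×0.1129)/96 = 0.001196 + 0.001565 = 0.002761; SE 5.25 points.
- Ratio 0.003242/0.002761 = 1.174; 288 × 1.174 = about 338 patients.

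**Equivalent number of patients analysed unadjusted, from the same 288.**

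| q | r | f = 25% | f = 50% | f = 75% |
|---|---|---|---|---|
| 15% | 90% | 311 | 338 | 371 |
| 15% | 70% | 298 | 308 | 320 |
| 10% | 60% | 291 | 295 | 299 |

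**Cross-check by simulation.** With 40,000 trials per setting, a Cochran-Mantel-Haenszel test on CT done or not was compared with one on the three CT levels. At q = 15% and r = 90%, power rises from about 92% to 93.4%, 94.9% and 96.3% for f = 25%, 50% and 75%. The variance ratios are 1.07, 1.16 and 1.27, against 1.08, 1.17 and 1.29 from the formula. Type I error in the null setting checked was 5.0%.

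**Sparseness.** At f = 50% and q = 15% the CT arm would hold 96×0.5×0.15 = about 7 CT-positive women, and 96×0.5×0.85×0.135 = about 5 to 6 non-standard treatments among CT-negative women. This limits the choice of model.

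**The case against.** The planned analysis is standard and valid. The trial is powered on the unadjusted test, the stated power is met, and further covariates could be added in a SAP that is not shown. All of that stands, which is why this is an improvement and not an error. It is still worth raising because Section 13.1 does name an adjustment set.

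The link is also softer than a rule. Table 5 gives recommendations; Section 8.1 leaves the final plan to the treating investigator; Section 1.6 notes that PET-CT may downstage; and category 2 also covers the distal vagina. This stands, and the 70% and 60% rows are there for it.

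Stage is already in the planned model, and Section 1.3 shows that it predicts para-aortic disease (7% in IB, 21% in IIB, 31% in III). Part of the gain may therefore be captured already. The check did not model stage, MRI or centre, so this stands as well.

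A reader might infer a much larger gain. If CT-positive women are made to account for nearly all non-standard treatment in the CT arm (5% among CT-negative, 90% among CT-positive), the same formula gives about 331, 389 and 471 patients. That needs (0.25 − 0.05)/(0.90 − 0.05) = 23.5% of women with a prior CT to be CT-positive at entry. The protocol points lower: 10 of the 25 points are palliative, and Section 12.1 expects women with distant metastases on a prior CT not to be referred, whereas "patients with a normal liver on CT prior to randomization would be referred to the trial".

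**Conclusion.** The point holds as a modest loss of efficiency. With 15% of prior CTs positive and 25% to 75% of women having one, the equivalent sample size is about 298 to 320 patients at a 70% link and 311 to 371 at a 90% link. In the low case it is about 291 to 299, which is next to nothing, and women without a prior CT add nothing. These figures rest on shares the protocol does not state, and they are measured against an unadjusted analysis, not against the planned adjustment for stage, MRI and centre.

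A reader might infer that the PET-CT effect is biased, because minimization balances only on whether a CT was done, or that the trial is underpowered. The documents support neither. Allocation balances CT findings on average, leaving only chance imbalance, and the recomputed power is 91.5%. Severity is low.

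**What to change.** Keep the unadjusted exact test as it is. In the adjusted analysis of Section 13.1, replace the yes/no CT factor by a prespecified three-level baseline factor:
- no prior CT;
- prior CT without disease beyond the standard pelvic field;
- prior CT with such disease.

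Code it from the report issued before randomization, without knowledge of allocation. Never code it from a CT done or repeated after randomization.

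Keep stage, MRI and centre in the same model. Because cells will be sparse, use penalised (Firth) logistic regression with small centres pooled by a rule set in advance. An exact test stratified on all four factors would break 96 controls into very small cells. Report the adjusted absolute difference with its 95% CI: the odds ratio itself changes when a strong covariate is added, so the gain in precision is read from the risk difference.

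The cost is one coded field from a report already held, a sentence in Section 13.1 or the SAP, and slightly sparser cells. No extra patients or scans are needed.
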